### Starling SV monitor procedure

Once the subject has been enrolled, either the investigator or researcher will proceed to place the Starling SV monitor on the subject. The Starling SV monitor will be connected to the subject by positioning four sensors from the system on the subject's chest: specifically, on the left and right upper and lower thorax. The device provides real-time data that can be observed on the monitor screen and is also stored internally. Fluid assessment can be instantly performed by examining the visible read-out on the monitor screen.

Prior to commencing the study, the device will be assessed to ensure optimal and expected hemodynamic readings can be obtained, following the guidelines outlined in the Starling SV

Instructions for Use (IFU). This step is crucial to ensure that the data collected from the monitoring devices will be valid and usable. It is recommended to allow approximately one minute for the device to auto-calibrate and establish a stable baseline before starting any measurements for the study data collection.

In the event that the Starling SV monitor does not provide the expected hemodynamic recordings, adjustments will be made. If necessary, the device will be replaced until the expected recordings are obtained. However, if it is determined that the device cannot provide the expected recordings, the subject will cross-over to the control arm and will be treated according to the standard care protocol.

**Fluid responsiveness assessment procedure**

A dynamic assessment of fluid responsiveness using the Starling SV monitor will be performed at every clinical decision point for the first three hours of study enrollment. (*see figure 1 'flowchart personalized protocol'*). Fluid responsiveness will be assessed in response to an IV fluid bolus of 500 mL in 10 min using the Starling SV hemodynamic monitor. To guide hemodynamic resuscitation, fluid responsiveness will be defined based on an increase in stroke volume in response to the fluid bolus.

**Data collection procedure**

The information recorded by the Starling SV will be collected and stored within the device, registered under the FLUIDS ID of the subject (coded). Once the data collection period ends, the data will be downloaded and stored for analysis. Other data collected by the researcher will be entered directly in REDCap. A full description and timeline of data collection is presented in **Table 1**.

| Study periods                                                                                                          | Screening*    | ED visit*       | General ward/ICU |            | Follow up |            |
|------------------------------------------------------------------------------------------------------------------------|---------------|-----------------|------------------|------------|-----------|------------|
|                                                                                                                        |               |                 |                  |            |           |            |
|                                                                                                                        |               | Baseline |                  |            |           |            |
| Hours/days                                                                                                      | Triage | 0h       | 24h       | 48h | 7d | 30d |
| Deferred consent                                                                                                       |               |                 |                  |            |           | x          |
| Review of in-/exclusion criteria                                                                                       | x             |                 |                  |            |           |            |
| Diagnosis of infection/sepsis (adjudication by an expert panel)                                                        | x             |                 |                  |            |           | x          |
| The presence of compression stocks                                                                                     | x             |                 |                  |            |           |            |
| Demographic data (i.e. age, sex, ethnicity, length, weight, BMI)                                                       |               | x               |                  |            |           |            |
| Medication use (i.e. cardiovascular, immunosuppressiva, diuretics)                                                     |               | x               | x                | x          |           |            |
| Co-morbidity (pre-existent, developing)                                                                                | x             |                 | x                | x          | x         | x          |
| Mortality (in-hospital, out-of-hospital)                                                                               |               |                 | x                | x          | x         | x          |
| Hospital admission (i.e. general ward, ICU)                                                                            |               | x               | x                | x          | x         | x          |
| Disease severity scores (i.e. SIRS, [q]SOFA, NEWS)                                                                     | x             | x               | x                | x          | x**       |            |
| Vital parameters (i.e. SBP, DBP, heart rate, respiratory rate, SpO2, temperature, GCS, CRT)                            | x             | x               | x                | x          |           |            |
| Lab values (i.e. leukocytes (including machine differential), thrombocytes, creatinin, bilirubin, CRP, albumin, ureum) | x             |                 | x                | x          | x         |            |
| Extended lab values (i.e. pH, lactate, NT-proBNP)                                                                      | x             |                 | x                |            |           |            |
| Organ support information (i.e. hemodynamic support, RRT, [non-]invasive mechanical ventilation, ECMO)                 | x             | x               | x                | x          | x         | x          |
| Volume of IV fluids (time, amount, type)                                                                               | x             | x               | x                | x          |           |            |
| Vasopressor therapy (time, amount, type)                                                                               |               | x               | x                | x          |           |            |
| (Elektro)physiological waveform data: (e.g.. PPG, ECG)                                                                 |               | x               |                  |            |           |            |
| PoCUS data (e.g. IVC diameter, collapsibility index, lung US)                                                          |               | x               | x                |            |           |            |
| Pre-tibial edema score                                                                                                 |               | x               | x                | x          |           |            |
| Cost-effectiveness data (i.e. costs and wins)                                                                          |               | x               |                  |            |           | x          |

**Table 1: description and timeline of data collection** \* Screening and ED visit occur on the same day. \*\* Follow up of severity scores is up to 7 days (or hospital ward discharge, whichever came first); hospital ward discharge comprises admission to the ICU or discharge home.

#### **8.4 Withdrawal of individual subjects**

Subjects can leave the study at any time for any reason if they wish to do so without any consequences. The investigator can decide to withdraw a subject from the study for urgent medical reasons.

##### **8.4.1 Specific criteria for withdrawal (if applicable)**

Not applicable.

#### **8.5 Replacement of individual subjects after withdrawal**

Subjects withdrawn from the study will be replaced by a subsequent patient that presents in the ED matching the inclusion criteria.

#### **8.6 Follow-up of subjects withdrawn from treatment**

After withdrawal of an individual subject from the study, all data, blood samples collected up to that point will be stored and kept in the database. Upon withdrawal, the subject from the intervention group will receive treatment according to the standard care UMCG-protocol, while the control group will continue with their existing treatment regimen. It is important to note that the measurements for the study will no longer be conducted for the withdrawn subject.

In the event that the participant does not provide consent or withdraws consent, it is up to the participant to indicate whether the data collected up to that point may be retained or must be destroyed.

#### **8.7 Premature termination of the study**

Not applicable.

## SAFETY REPORTING

### 8.8 Temporary halt for reasons of subject safety

In accordance to section 10, subsection 4, of the WMO, the sponsor will suspend the study if there is sufficient ground that continuation of the study will jeopardise subject health or safety. The sponsor will notify the accredited METC without undue delay of a temporary halt including the reason for such an action. The study will be suspended pending a further positive decision by the accredited METC. The investigator will take care that all subjects are kept informed.

### 8.9 AEs, SAEs and SUSARs

#### 8.9.1 Adverse events (AEs)

Adverse events are defined as any undesirable experience occurring to a subject during the study, whether or not considered related to the intervention procedure. All adverse events reported spontaneously by the subject or observed by the investigator or his staff will be recorded.

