#### Safety

- To examine the occurrence of adverse events related to the use of a personalized hemodynamic resuscitation protocol within 48 hours and 7 days.
- To assess the rate of acute kidney injury associated with the use of a personalized hemodynamic resuscitation protocol within 48 hours and 7 days.

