|                                    |                                                                                                                                                                                                                                                                                                                                                                                                                                                                                                  |
|------------------------------------|--------------------------------------------------------------------------------------------------------------------------------------------------------------------------------------------------------------------------------------------------------------------------------------------------------------------------------------------------------------------------------------------------------------------------------------------------------------------------------------------------|
| Acute kidney injury                | 
 
• AKI based on KDIGO criteria within 48 hours
 
• AKI based on KDIGO criteria within 7 days
 
• Change in Serum Creatinine Levels from Baseline to 48 hours
 
• Change in Serum Creatinine Levels from Baseline to day 7 (or hospital discharge, whichever came first)
 
• Requirement for renal replacement therapy (RRT) within 7 days
 
• Requirement for renal replacement therapy (RRT) within 30 days
 
 |
| Major Adverse Cardiac Event (MACE) | Any of the following within 30 days: 
 
• Cardiovascular death
 
• Nonfatal myocardial infarction
 
• Nonfatal stroke
 
                                                                                                                                                                                                                                                                                                               |

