## 8.3 Study procedures

### Screening and enrollment

Patients will be recruited by the FLUIDS research team. First, ED physician and/or nurse will screen all patients entering the ED for potential inclusion in the study, specifically between 9 am and 5 pm during all weekdays. If a patient is eligible for participating in the study, the ED physician/nurse will promptly notify a FLUIDS-researcher present at the ED. Subsequently, this researcher will approach and enrol the eligible patient, being actively involved in the initial assessment and providing recommendations to the attending physician regarding hemodynamic resuscitation.

The FLUIDS research team will consist of fully trained individuals with a medical background and research affinity. Prior to the study start, the research team will undergo comprehensive training on utilizing the Starling SV monitor, interpreting results and conducting PoCUS measurements. Additionally, a follow-up procedure will be established, where the research team is responsible for implementing the Starling SV monitor protocol during subsequent assessments.

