#### 8.9.2 Serious adverse events (SAEs)

A serious adverse event is any untoward medical occurrence or effect that

- results in death;
- is life threatening (at the time of the event);
- requires hospitalisation or prolongation of existing inpatients' hospitalisation;
- results in persistent or significant disability or incapacity;
- is a congenital anomaly or birth defect; or
- any other important medical event that did not result in any of the outcomes listed above due to medical or surgical intervention but could have been based upon appropriate judgement by the investigator.

An elective hospital admission will not be considered as a serious adverse event.

All SAEs will be evaluated and recorded if relationship is unknown or if SAE is related to study procedures. The sponsor will report the SAEs through the web portal *ToetsingOnline* to the accredited METC that approved the protocol, within 7 days of first knowledge for SAEs that result in death or are life threatening followed by a period of maximum of 8 days to complete the initial preliminary report. All other SAEs will be reported within a period of maximum 15 days after the sponsor has first knowledge of the serious adverse events.

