**8.11 Follow-up of adverse events**

All AEs will be followed until they have abated, or until a stable situation has been reached. Depending on the event, follow up may require additional tests or medical procedures as indicated, and/or referral to the general physician or a medical specialist. SAEs need to be reported till end of study within the Netherlands, as defined in the protocol.

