#### 11.2.1. Recruitment and consent method

1. Upon ED admission, one of the researchers identifies potential study participants meeting the inclusion criteria by information provided by the treating physician. If possible, the patient and/or his/her designated proxy is informed about the study by the researcher, and their consent is sought. If a patient and/or his/her designated proxy does not orally refuse to participate, the patient will be recruited for the study.
2. Once recruited, the patient is randomized according to the study protocol and informed about the randomization results. Following randomization, treatment is promptly initiated as per protocol.
3. The patient themselves and/or his/her designated proxy will be asked to provide deferred consent (DC) within 30 days of the study start. Information about the study will be provided as soon as possible after study entry, which may be at the ED, ICU, or general ward in hospital. If the subject regains mental competence and is capable, their deferred consent for the continuation of their participation in the study must be obtained without undue delay. In cases where the patient is discharged from the hospital and no consent have been obtained, they may be contacted up to three times, and a letter is mailed to obtain deferred consent. Data collection is carried out for a maximum of 30 days from the time of ED arrival. All contact moments will be registered in REDcap' screening field of 'deferred consent'.
4. If the subject does not provide deferred consent, they must be actively informed of the deletion of data previously collected in the study. Throughout the study, participants who signed deferred consent retain the right to withdraw at any time. However, by signing deferred consent, they grant permission to use their collected data for research purposes up to the point of withdrawal.
5. In accordance with the CCMO guidelines on 'deferred consent' in emergency research situations, if a patient passes away before deferred consent is obtained within the 30-day limit, consent for data use is assumed and not sought from legal representatives due to the following reasons:
  - a. Relatives do not have an independent right to review or assess therapeutic or research data as they are no longer legal representatives.
  - b. The patient's wishes cannot be formally established post-mortem, and relatives no longer have a formal role as representatives in the research context.

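### The adverse-event objective (48 hours and 7 days) has no overall endpoint in 8.1.2 and no row in Table 1, and it rests on unsolicited capture that may differ between open arms

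*Protocol*

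**What the plan says.** - **Objective.** The first safety objective in Section 2 is "To examine the occurrence of adverse events related to the use of a personalized hemodynamic resuscitation protocol within 48 hours and 7 days".
- **Endpoints.** The Safety table in 8.1.2 covers congestion and heart failure, respiratory insufficiency/ARDS, kidney injury and RRT, MACE, vasopressor therapy and mortality, nearly all with stated windows (for example "AKI based on KDIGO criteria within 48 hours"). It has no line for any AE or any SAE.
- **Data schedule.** Section 8.3 states "A full description and timeline of data collection is presented in" Table 1. No row of Table 1 is for adverse events. The nearest is co-morbidity, pre-existing or developing, at triage, 24h, 48h, 7d and 30d.
- **Capture.** Section 8.9.1 defines an AE irrespective of relation to the intervention and then says "All adverse events reported spontaneously by the subject or observed by the investigator or his staff will be recorded". For serious events, 8.9.2 says "All SAEs will be evaluated and recorded if relationship is unknown or if SAE is related to study procedures".
- **Contact with trial staff.** The trial is open (8.2). The minimum vital-sign schedule in the first three hours is the same in both arms (5.1). The guided arm also has a monitor assessment at each decision point in those three hours (5.1, 8.3), and "the research team is responsible for implementing the Starling SV monitor protocol during subsequent assessments".
- **Time limits.** Section 8.11 says "SAEs need to be reported till end of study within the Netherlands, as defined in the protocol", and 11.5 defines the end of study as the last patient's last visit. Section 11.2.1 says "Data collection is carried out for a maximum of 30 days from the time of ED arrival".

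**The concern.** A stated safety objective needs a defined endpoint and data collected in the same way in both arms. Here the overall AE count has neither. What is recorded depends on a patient volunteering an event or on someone from the trial seeing it. Section 10.3 allows incapacitated patients to be enrolled, and they cannot volunteer anything. In an open trial with more research-team contact in one arm, the AE comparison may then partly measure contact rather than harm. It could suggest an excess in the guided arm or hide one in controls. An event that was never recorded may not be recoverable later.

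The wording of the objective adds a second problem. Control patients do not receive the personalised protocol, so an event related to it has no control counterpart. The count also depends on an unblinded judgement of relatedness.

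**Working it through.** **1. Is there an endpoint or a scheduled record behind the objective?** Section 2 names AEs at 48 hours and 7 days. No line in the 8.1.2 Safety table and no row of Table 1 records AEs overall. The windows exist in Section 2, but the endpoint and the scheduled data do not.

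**2. Which events are exposed?** Events with their own 8.1.2 lines have the same definitions and time points in both arms, and Table 1 schedules labs, organ support, edema score and mortality without distinction of arm. Events left to 8.9.1 alone include arrhythmia (MACE is limited to cardiovascular death, infarction and stroke), extravasation, and skin irritation, which the protocol itself names as a device risk (10.4, 12.2).

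**3. How long does the documented extra contact last?** Three hours, which is 3/48 = 6.3% of the 48-hour window and 3/168 = 1.8% of the 7-day window.

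**4. What could unequal detection do?** The plan gives no AE rate and no detection rate, so there is no plan figure to reproduce. The only input from the protocol is 94 per group (4.4). The rest is assumed: the same true proportion p with at least one AE in both arms, detection c in control and g in guided, and a two-sided pooled two-proportion test at 0.05. The protocol sets no such test for overall AEs.

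- Observed rates are p·c and p·g, so the observed risk ratio is g/c.
- With d = p(g − c), mean rate m, SE0 = √[2m(1 − m)/94] and SE1 = √[(a(1 − a) + b(1 − b))/94] for observed rates a and b, the chance of p < 0.05 is Φ[(d − 1.96·SE0)/SE1] + Φ[(−d − 1.96·SE0)/SE1].

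*Detection gap over the whole window, 60% v 80%, p = 40%.* Observed 24% v 32%, RR 0.80/0.60 = 1.33. SE0 = 0.0655, SE1 = 0.0652. Φ[(0.08 − 0.1284)/0.0652] = Φ(−0.74) = 0.229; the other tail is about 0.001. Total about 23%.

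*Detection gap confined to the first three hours, p = 40%.* Assume 25% of AEs arise then, detected at 60% v 80%, with 70% detection in both arms afterwards. Control: 0.25 × 0.60 + 0.75 × 0.70 = 0.675. Guided: 0.25 × 0.80 + 0.75 × 0.70 = 0.725. Observed 27% v 29%, RR 1.07. Φ(−1.66) + Φ(−2.27) = 0.049 + 0.012, about 6%.

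| Assumed detection, control v guided | Observed RR | False positives at true rate 20% | 40% | 60% |
|---|---|---|---|---|
| equal | 1.00 | 5% | 5% | 5% |
| 67.5% v 72.5% | 1.07 | 5% | 6% | 7% |
| 70% v 80% | 1.14 | 7% | 9% | 13% |
| 60% v 80% | 1.33 | 12% | 23% | 38% |

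**5. Relatedness.** Section 2 counts events related to the guided protocol, 8.9.1 records events whether related or not, and 8.9.2 makes the recording of SAEs conditional on a related or unknown relationship. The three rules give different counts.

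**6. SAE period.** If end of study in 8.11 carries the 11.5 meaning, SAE reporting for a patient enrolled early in a trial expected to last 12 months (Section 3) would run far beyond the 30-day data limit.

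**The case against.** The strongest reply is that the important harms do not depend on 8.9.1. Congestion, respiratory failure, kidney injury, MACE, vasopressor use and death are separate endpoints with scheduled data in both arms. This stands, and it limits the point to the remaining, mostly milder events.

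A reader might infer that the guided arm will show more events. The documents do not support that. Minimum bedside observation is identical, a researcher takes part in every enrolled patient's initial assessment (8.3), sensor placement is not limited to one arm in 4.1 or 8.3, and the documented extra contact ends after three hours. A reader might also take 23% as the expected false-positive rate. It needs a 60% v 80% gap over the whole window, which nothing in the protocol establishes.

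It can also be said that the AE definition, the analysis windows, the SAE reporting period and the data limit serve different purposes and can nest. That is fair for most of them. Only the SAE end-of-study wording against the 30-day limit needs tidying.

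The reply does not remove the main gap. Even with equal detection, the stated objective has no overall endpoint and no scheduled record. Leaving the analysis of binary endpoints to a later plan (9.2) does not supply data that were never collected.

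**Conclusion.** The point holds in a limited form. The overall AE objective has windows but no endpoint in 8.1.2 and no data row in Table 1. Its capture rule may detect events unequally in an open trial. The exposure lies in events outside the existing 8.1.2 safety lines.

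Neither the size of any bias nor its presence can be established from the documents. At a true rate of 40% and 94 per arm, it ranges from negligible (RR 1.07, about 6% false positives, if the detection gap is confined to three hours as assumed above) to material (RR 1.33, about 23%, if a 60% v 80% gap applied throughout). The relatedness conflict between Section 2 and 8.9.1 is plain on the text and depends on no assumption. The change should be made because it is cheap and lets the trial answer its own objective.

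**What to change.** 1. Add an AE/SAE row to Table 1 at 48h and 7d, completed in both arms by the same structured chart review against one fixed list, whoever first noticed the event. The list should cover events that 8.1.2 does not already define.
2. Add to the 8.1.2 Safety table the proportion with at least one AE, and with at least one SAE, by 48 hours and by 7 days, regardless of relatedness. Base the between-arm comparison on these.
3. Report sensor-site skin reactions separately as a device event. If only guided patients wear sensors, including them would create an arm difference by construction.
4. Report spontaneously reported or observed events as a listing only.
5. Reconcile the relatedness wording of Section 2 with 8.9.1, and bring the SAE recording rule in 8.9.2 into line so that the SAE proportion can be computed.
6. Reconcile the SAE period in 8.11 with the 30-day limit in 11.2.1.

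Cost: one form row at two existing time points, some wording, and extra chart-review time per patient. Treatment and sample size do not change. Chart entries are still made by unblinded staff, so the review reduces unequal detection but cannot guarantee its absence.
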